## Abstract

**Background:**

Current guidelines for dementia care recommend the combination of drug therapy with non-pharmaceutical measures like counselling and social support. However, the scientific evidence concerning non-pharmaceutical interventions for dementia patients and their informal caregivers remains inconclusive. Targets of modern comprehensive dementia care are to enable patients to live at home as long and as independent as possible and to reduce the burden of caregivers. The objective of the study is to compare a complex intervention including caregiver support groups and counselling against usual care in terms of time to nursing home placement. In this paper the study protocol is described.

**Methods/Design:**

The IDA (Initiative Demenzversorgung in der Allgemeinmedizin) project is designed as a three armed cluster-randomized trial where dementia patients and their informal caregivers are recruited by general practitioners. Patients in the study region of Middle Franconia, Germany, are included if they have mild or moderate dementia, are at least 65 years old, and are members of the German AOK (Allgemeine Ortskrankenkasse) sickness fund. In the control group patients receive regular treatment, whereas in the two intervention groups general practitioners participate in a training course in evidence based dementia treatment, recommend support groups and offer counseling to the family caregivers either beginning at baseline or after the 1-year follow-up. The study recruitment and follow-up took place from July 2005 to January 2009. 303 general practitioners were randomized of which 129 recruited a total of 390 patients. Time to nursing home admission within the two year intervention and follow-up period is the primary endpoint. Secondary endpoints are cognitive status, activities of daily living, burden of care giving as well as healthcare costs. For an economic analysis from the societal perspective, data are collected from caregivers as well as by the use of routine data from statutory health insurance and long-term care insurance.

**Discussion:**

From a public health perspective, the IDA trial is expected to lead to evidence based results on the community effectiveness of non-pharmaceutical support measures for dementia patients and their caregivers in the primary care sector. For health policy makers it is necessary to make their decisions about financing new services based on strong knowledge about the acceptance of measures in the population and their cost-effectiveness.

**Trial registration:**

ISRCTN68329593

## Background

Dementia care is one of the most important challenges for health care systems in the greying societies of – for example – the US or Europe. Based on epidemiological prognoses they will have to cope with doubled or tripled figures of dementia patients until 2050 [1-3]. In Germany, direct medical costs for patients with dementia totalled 6.1 billion Euros in 2004 which made up 2.7% of total direct medical cost. Institutional care for patients with dementia accounted for 3.9 billion Euros [4]. Hallauer and colleagues calculated that the average total costs per patient including informal care sum up to approximately 44,000 Euros per year in Germany, of which the monetary equivalent of informal care giving time is the largest share [5]. From a societal and public health point of view, there is need to implement evidence based standards and services of medical and social care for patients and their caregivers [3].

Looking at current clinical dementia guidelines, there seems to be sufficient evidence for the efficacy of some drugs (e.g. cholinesterase inhibitors) in symptomatic therapy aiming at the delay of the disease progress. However, the scientific evidence concerning non-pharmaceutical interventions for dementia patients and their informal caregivers remains inconclusive [6-15]. Reasons can be found in the heterogeneity of intervention types, populations, settings, study designs, outcomes and – in addition – in widespread methodological quality problems, e.g. small sample sizes, observation periods too short to see clinically relevant intervention effects, and further shortcomings of scientific evaluation [6,7]. In a recently published meta analysis, an overall significant positive effect of non-pharmacological interventions in delaying institutionalization was reported, but there was significant heterogeneity between the thirteen studies [16]. While the cost-effectiveness of anti-dementive drugs is frequently analyzed, only few economic evaluations exist for non-medical interventions aiming to postpone institutional care [17-23].

Because in Germany general practitioners (GPs) play the key role in health care of the elderly, they automatically come into focus when introducing new services in dementia care. In most cases GPs are primarily faced with essential tasks like detecting and diagnosing dementia, information of patient and family members, drug therapy, and linking to further counselling and supportive measures. Especially in the care of non-institutionalized dementia patients, the GPs' influence on the help seeking behaviour of patients and caregivers can be decisive for families' willingness to accept external support and expert counselling. A systematic interdisciplinary collaboration between GPs, medical specialists and professionals in the field of social and psychological dementia care will be a key issue in the future [24].

In current practice the context of dementia care is difficult and study results [25-31] hint on the existence of a bundle of factors related to patient, caregiver, and physician which are building a barrier for optimizing dementia care.

On the societal level, dementia is a stigmatized disease surrounded by influences of ageism. Patients and caregivers often deny dementia symptoms, experience difficulties in accepting the diagnosis, and react to the disease with social withdrawal and depression. They have a lack of disease specific knowledge and of information on regional support and counselling services. This lack of knowledge is often shared by their GPs [32] who have a tendency of tabooing cognitive impairments and have difficulties in telling bad news – especially disclosing a diagnosis of dementia [33-36]. Furthermore, a skeptical or negative attitude towards the potential benefits of dementia drug therapies [37] and the unclear evidence concerning non-pharmaceutical treatment and support options as well as unclear referral ways to specialist psychiatric services (e.g. memory clinics) may prevent the optimal care for dementia patients.

All these above mentioned factors in sum lead to delayed and insufficient care with regard to diagnostics, treatment, counselling and social support for many dementia patients [3,26]. Therefore, a potentially successful intervention program in primary care has to address several of these obstacles to optimize dementia care. Focussing on single factors like education and training programs for doctors or distribution of dementia guidelines to close GPs' knowledge gaps probably is not enough [38-40].

The IDA study aims to combine several treatment options including training of GPs concerning diagnosis and treatment of dementia, out-patient specialist support for GPs, the offer of support programs and counseling for informal caregivers of patients with dementia.

The main research questions of the IDA project, from the perspectives of health care and health economics, are: (1) Is a complex intervention for community dwelling dementia patients, their caregivers and doctors more effective than usual care with respect to postponement of nursing home placement? (2) Does the intervention have an effect on disease progression and on caregiver burden? (3) Is the intervention cost-effective compared to usual care when assessed from the societal perspective? The objective of this paper is to describe the study protocol of the cluster-randomized IDA study. Recruitment and follow-up of all study patients have ended and the analysis phase has started by spring 2009. The detailed description of the study background and protocol is published as a reference for forthcoming papers describing the study results.

## Methods/Design

### Study Design and Setting

The IDA study is designed as a three-armed cluster-randomized trial. The main research hypothesis is that for dementia patients still living at home a complex intervention consisting of an initial training of GPs in evidence based diagnosis and treatment, of the provision of caregiver support groups, and of actively approaching family counselling, can prolong time to nursing home placement in comparison to usual care. In comparison to usual care (study arm A), one intervention group receives additional training of GPs in medication and non-medication based therapies for dementia, and caregivers are offered to participate in caregiver support groups (study arm B), whereas in the second intervention group actively approaching family counselling is additionally implemented (study arm C). The duration of the intervention phase is two years. However, a change of study design became necessary due to the unexpected slow recruitment of patients (18 months instead of 6 months) and the very low participation rates of caregivers in the caregiver support groups. The main focus of the study was shifted towards the comparison of groups A and C. In group B, the actively approaching family counselling was implemented after the 1-year follow-up. Thereby, patients in arm B can serve as an intermediate intervention group in the first year and as an additional full intervention group in the second year. The new study design is shown in Figure 1.

**Figure 1 F1:**
[figure not shown]
**Study design**.

The study region Middle Franconia is a mixed urban rural area around Nuremberg in Bavaria, Germany.

### Recruitment of GPs and Patients

All GPs in the study region in Middle Franconia (about 1200) were contacted with an information leaflet and invited to participate in the project. GPs willing to participate had to sign a contract with the AOK sickness fund. The training sessions (one for each GP) took place with groups of 10 to 30 GPs.

After the training, the GP identified all dementia patients in his or her practice who fulfilled the following selection criteria. Patients were included if they had mild to moderate dementia as defined by an MMSE (Mini Mental State Examination) between 10 and 24 [41], if they were at least 65 years old and a member of the AOK health insurance, and if they still lived at home and had an informal caregiver who was willing to participate in the study. The MMSE is a widely used test of cognitive function. Patients with a MMSE score below 10 were excluded because they were considered to be unable to give informed consent. In addition, we expected that in these patients nursing home placement could be necessary before treatment could have any effect. Patients with a MMSE score above 24 were excluded to gain a certain level of diagnostic accuracy and reduce the rate of falsely included patients with mild cognitive impairment (MCI), because a differential diagnosis is often difficult for GPs. Patients were excluded if they had terminal illness or if admission to nursing home was already planned. Patients not able or not willing to give informed consent were also excluded. Patients could be newly diagnosed or were already known as dementia patients.

Signed informed consent of study participants and their informal caregivers was required before patients could be entered into the study. The study protocol as well as the amendment necessitated by the change in study design has been approved by the Ethics Committee at the Bavarian Chamber of Physicians. (Date of approval: 30/05/2005, Reference number: 05029). Furthermore, the study is conducted in accordance to German privacy law and in compliance with the Helsinki Declaration. Recruitment of patients started in June 2005 and ended in December 2006.

### Randomization

The IDA project is a cluster-randomized study where the general practices are the clusters and thus the units of randomization. If two or three GPs from the same group practice wanted to participate in the study and attended the training course, they were randomized into the same study arm. The randomization was done by the statistics and data centre, usually one day before each training course when the full list of registered participants was available. We applied the randomization method of permuted blocks within strata, where stratification was done with respect to study region and type of practice (single vs. group). The allocation ratio was 1:1:1. The GPs were informed about their assigned study arm during the training course.

### Interventions

The study arm A serves as a control group where patients receive usual care. However, since GPs served as mediators of the intervention in IDA, all participating GPs received at least basic information concerning dementia diagnosis and about study procedures.

#### Training GPs

The obligatory training course for all participating GPs consisted of a dementia-specific part and a part concerning the study.

The dementia-specific part of the training consisted of dementia diagnostics including execution of the Mini-Mental Status Examination (MMSE) with a video demonstration and a section about patient and caregiver information (120 minutes). Afterwards, the GPs were informed to which study arm they were randomized. GPs of study arm A were separated from B and C and received study-specific information. Group A physicians were trained in early detection and diagnosis of dementia only. Their knowledge of non-medical treatment options and drugs was not part of the initial training. As a comparator this level of knowledge could serve as a proxy for the general status quo. The diagnostic training contained basic information about dementia (epidemiology, pathophysiology, early symptoms of dementia), anamnesis and physical examination, laboratory diagnostics, and psychometric tests. The additional training for group B and C physicians on treatment of dementia (140 minutes) consisted of information about interfaces in the German health care system, non-medication based treatment, information and counselling of caregivers, medical treatment options, therapy of non-cognitive disorders and specific problems. The dementia guideline for GPs, published by the Witten-Herdecke University  and the therapy recommendations of the Pharmaceutical Commission of the German Medical Association were used as the basis of the training. The therapeutic and diagnostic part of the training was given by five neurologists or psychiatrists with proven gerontopsychiatric expertise who are active in out-patient care in the study region.

All doctors received a folder containing written information specific to groups A, B, or C of the study including the slides of the training, the current dementia guideline and the baseline documentation forms for 10 patients.

#### Out-patient specialist support for GPs

The medical experts involved in the training offered out-patient consultant support to the GPs in groups B and C. In the case of acute deterioration or problems with therapy, appointments were available for dementia patients at short notice. Additionally a weekend telephone consultant on-call service was set up for the GPs.

#### Recommending family caregiver support groups

In groups B and C, the GPs suggested that caregivers should attend a family caregiver support group. The caregiver received an information sheet from the GP with contact details of 17 family caregiver support groups within the study region, all of which had been set up independently from the IDA project. The groups were required to have three qualifying characteristics: (1) professional supervision, (2) hold at least ten formal meetings per year, and (3) contain a psycho-educational element to improve the competencies of the family caregivers. After the consultation, the GP sent a fax to the chosen family caregiver support group, so that it would be possible to verify later which relatives attended a support group following the GP's offer. The family caregiver alone decided whether the visit actually took place or not.

#### "Counsellors contact caregivers" (CCC)

The family caregivers in Group C (and in group B after one year as well), were offered a special type of family caregiver counselling which would be recommended to them by their GP. After receiving the registration fax from the GP, the counsellor (now referred to as the "IDA counsellor") contacted the family caregiver by phone and tried to establish personal contact in form of a home visit, if possible. The IDA counsellor used elements of case and care management in educating and supporting the family caregivers psychologically and socially, to improve their competences in all facets of care. The aim was to support the family caregiver to the extent that the dementia patient was able to remain in the domestic environment as long as possible. Guidelines were developed for choosing those supportive measures that were expected to have a positive effect in specific situations. The IDA counsellor was also available by phone on weekends.

Four IDA counsellors worked in the project. Their professional competence consisted of training and several years of experience in nursing. They were expected to be able to empathise with the family caregivers and they received regular training in subjects important for the counselling process. Because of the large study area, the care managers were assigned to the patients regionally.

### Measurements

The study outcome variables concern potential effects of the intervention on the patient and on the caregiver level. In addition, economic outcomes from a societal perspective are registered.

The primary endpoint of the study is the remaining time the patient lives at home. This is defined as time from study entry until either nursing home placement (for at least 8 weeks) or death. In an additional analysis, death will be treated as a censoring event.

Secondary endpoints are:

1. Cognitive functioning of the patients (MMSE)

2. Patients' ability to perform ADL and IADL measured by the Barthel-Index [42] and the IADL subscale of the Nurses' Observation Scale for Geriatric Patients NOSGER [43]

3. Subjective burden of informal caregivers measured by the Burden Scale for Family Caregivers (BSFC) [44]

4. Quality of life of the patients (EQ-5D) [45-47]

5. Time to death

6. Number and duration of hospital stay

7. Direct medical and non-medical costs (including informal care)

8. Use of formal care and support services

Table 1 gives an overview on baseline and follow-up measurements. The measurements in the IDA project occur at the following fixed and variable time points: baseline measurement at entry into study (t_0_), follow-ups at six months (only for patients in arm B and C if they receive an antidementive drug) (t_6_), at twelve months (t_12_) and after 24 months (t_24_). If the patient was admitted to nursing home, no further assessments took place but GPs and caregivers were asked about the reasons for the institutionalization.

**Table 1 T1:** Baseline and follow-up measurements

Aim	Instrument	Applied to	t_0_	t_6_	t_12_	t_24_	t_h_
Anamnestic data	Baseline CRF	GP	X				

Quality of life of patient	EQ-5D	Patient, informal caregiver and GP	X		X	X	

Cognitive function patient	MMSE	GP	X	X	X	X	

	DEMTECT	GP	X				

Evaluation of antidementiva therapy	CRF	GP		X			

Global health status of the patient	CGI	GP	X	X	X	X	

Behavioural problems patient	NOSGER (Subtest)	Informal caregiver	X		X	X	

ADL patient	Barthel-Index	Informal caregiver	X		X	X	

IADL patient	NOSGER (Subtest)	Informal caregiver	X		X	X	

Caregiver burden	BSFC	Informal caregiver	X		X	X	

Resource use, situation of caregiver	Questionnaire	Informal caregiver	X		X	X	

Nursing home placement (reasons)	Questionnaire	Informal caregiver and GP					X

The baseline assessment (t_0_) consisted of the documentation by the GP including test results and a telephone interview with the primary caregiver. In accordance with a naturalistic study design, documentation was restricted to an essential set of variables. The computer-aided telephone interview with the informal caregiver was conducted by trained interviewers. Apart from the Barthel-Index, NOSGER, and BSFC items, the telephone interview contains detailed assessment of informal care time and the use of formal care by home care services. If the interviewees refused to respond by telephone, they were asked to answer a written version of the questionnaire.

### Economic data

The cost-effectiveness of the intervention will be calculated from a societal perspective. Table 2 shows the different data sources for the assessment of resource use and direct cost. All patients, as well as caregivers who are insured with the same sickness fund, were asked to give permission to get their health insurance data over a time period covering one year before and four years after study entry.

**Table 2 T2:** Data sources for cost estimation

*Category*	*Source*
Outpatient care	Health insurance data

Prescribed drugs	Health insurance data

Inpatient care	Health insurance data

Rehabilitation	Health insurance data

Medical aids and non-physician services	Health insurance data and caregiver interview

Informal care	Caregiver interview

Other dementia-related costs not reimbursed by the health insurance including self-paid drugs	Caregiver interview

Formal care and support services	Health insurance data and caregiver

The informal care time of all involved caregivers is assessed within the telephone interview with the primary caregiver. We used an extended version of the specific questions on informal care time of the Resource Utilization in Dementia (RUD)-instrument [48,49]. Formal and informal care was assessed by days during the last four weeks and average number of hours on these days. Costs not reimbursed by the health insurance were additionally assessed.

Intervention costs will be estimated, these include costs for care managers (including labour costs and overhead costs) and for caregiver support groups. Study specific costs, which would not occur in routine application, will not be considered.

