### Economic evaluation

The primary economic evaluation will be a cost-effectiveness analysis from the societal perspective. The results will be presented as incremental cost per additional year living at home. We will use the bootstrap approach to calculate confidence intervals for incremental cost-effectiveness ratios. In a secondary cost-utility analysis, quality-adjusted life years (QALYs) will be calculated based on EQ-5D values.

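### Informal-care cost is measured only at entry, month 12 and month 24 and lost around the event; the stated available-case rule, if applied to costs, selects the comparison on the outcome

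*Protocol article*

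**What the plan says.** **Importance of the item.** The Background cites an average total cost of about 44,000 Euro per patient-year in Germany, "of which the monetary equivalent of informal care giving time is the largest share". Under Economic evaluation, the primary analysis takes the societal perspective: "The results will be presented as incremental cost per additional year living at home". Direct costs including informal care are secondary endpoint 7.

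**How it is measured.** Table 2 names the caregiver interview as the only source for informal care. Under Economic data: "The informal care time of all involved caregivers is assessed within the telephone interview with the primary caregiver", and "Formal and informal care was assessed by days during the last four weeks and average number of hours on these days". In Table 1 the row "Resource use, situation of caregiver" is marked at t0, t12 and t24, and at neither t6 nor the placement contact (t_h).

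**What happens at the event.** Under Measurements: "If the patient was admitted to nursing home, no further assessments took place but GPs and caregivers were asked about the reasons for the institutionalization".

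**What is planned for the gaps.** The Analysis section says that most secondary endpoints will have no measurement once a patient has died or moved to a nursing home. It therefore plans to analyse available cases. Imputation is an additional analysis and names only patients admitted to a nursing home.

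**The concern.** Insurance costs run continuously up to the event, but informal care does not. It is seen in short windows a year apart, and observation stops at the event that defines the effectiveness outcome. The stretch of home care just before placement or death is never observed unless a scheduled interview happens to fall there. The placement contact reaches the caregiver but does not ask about care time.

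The number of patients without follow-up information therefore depends on the event rate, which the intervention is meant to change. If informal-care cost is handled by the available-case rule, patients enter the cost comparison because they stayed at home. The additional imputation does not name deaths, although death is part of the primary endpoint. At stake is the cost side of the primary economic result; the test of time at home is untouched.

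**Working it through.** **Inputs.** Proportions still at home at two years: A 50%, B 65%, C 80% (Sample size). Revised A versus C assumption: a 20-point difference, base rate not stated (Sample size), so I show 50/70 and 60/80. Recruited: 390 patients (Abstract), about 130 per arm if split evenly (my assumption). The spread of events over the two years is not given; I assume a constant hazard and then vary it.

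**1. The plan's own figure.** For 50% versus 65%, two-sided 5%, power 90%, pooled variance:
n = [1.960 × √(2 × 0.575 × 0.425) + 1.282 × √(0.25 + 0.2275)]² / 0.15² = (1.370 + 0.886)² / 0.0225 ≈ 226.2, rounded up to 227. Then 227 × 1.2 = 272.4. The stated 227 and 272 reproduce, so the planning rates are used as the plan means them.

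**2. Coverage.** The entry window lies before study entry, so follow-up has two four-week windows: 8 / 104 weeks = 7.7%.

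**3. Patients with no follow-up value.** With S the proportion at home at two years, the share with an event before month 12 is 1 − S^0.5. The year-2 share is S^0.5 − S.

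| S | Event in year 1 (entry value only) | Event in year 2 (nothing after t12) |
|---|---|---|
| 50% (A) | 29.3% | 20.7% |
| 65% (B) | 19.4% | 15.6% |
| 80% (C) | 10.6% | 9.4% |

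The A/C ratio in year 1 is 2.8. Weibull shapes from 0.75 to 2 move A between 34% and 16% and C between 12% and 5%, with the ratio at 2.7 to 2.9.

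**4. Revised 20-point difference, constant hazard.** 50/70: 29.3% versus 16.3%, ratio 1.8. 60/80: 22.5% versus 10.6%, ratio 2.1. With no effect the ratio is 1.

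**5. In patients.** At 130 per arm: 38 in A versus 14 in C (50/80), 38 versus 21 (50/70), or 29 versus 14 (60/80).

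**6. Share of home time concerned.** With λ = −ln(S)/2 per year, mean home time over two years is (1 − S)/λ. Home time contributed by patients with a year-1 event is (1 − e^−λ)/λ − e^−λ.
- S = 50%: 0.138 / 1.443 = 9.6%
- S = 60%: 0.108 / 1.566 = 6.9%
- S = 70%: 0.079 / 1.682 = 4.7%
- S = 80%: 0.052 / 1.793 = 2.9%

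The home time valued from the entry interview alone is thus a minority, but unequal between arms if the planned effect exists.

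**7. Who is left at month 24.** An available-case comparison at t24 would contain, before other losses, 50% of A and 80% of C under the planning rates.

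**The case against.** **The analysis plan may settle this.** How costs accumulate between interviews is normally left to the full protocol or analysis plan, and its absence from an article is no finding. That stands. What remains is stated in the article: the measurement times, the lack of care-time questions at placement, the available-case rule for most secondary endpoints, and an imputation that names only nursing home cases. The article does not say that the rule covers costs, so that part is conditional.

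**Arm A need not have many more such patients.** A reader might take this as a fact. It is an expectation under the planning effect; no document reports event counts, and without an effect there is no imbalance.

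**A bias in Euro against the intervention is not established.** A reader might infer one as follows. Carry entry values forward, let care rise linearly to k times baseline by the event, and price informal care at half of 44,000 Euro per year, 22,000 / 12 ≈ 1,833 Euro per month. Missed care per patient is (k − 1)/2 times the home months of year-1 event patients. For k between 1.25 and 2 that is 0.207 to 0.828 baseline-months in A and 0.078 to 0.311 in C (50/80). The difference is 0.129 to 0.517 months, or about 240 to 950 Euro; at 50/70 it is about 160 to 650 Euro. The article supports none of the three premises:
- It plans no carry-forward.
- It gives no course of care before an event. The Discussion notes that placement may have causes unrelated to the progress of dementia, such as a caregiver's death. At k = 1 the bias is zero; below 1 it changes sign.
- It says only that informal care is the largest share, not half.

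Even 950 Euro is about 1.1% of 2 × 44,000 = 88,000 Euro.

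**The entry value is not wholly pre-intervention.** It precedes counselling, but GP training came before patients were identified.

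**Costs are secondary and documentation was deliberately lean.** This is true and limits the weight of the point.

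**Conclusion.** The concern holds as a limitation of measurement combined with an unsuitable missing-data rule. The cost item cited as the largest is observed in 8 of 104 follow-up weeks, and patients with a year-1 event have no follow-up value. If the stated rule for secondary endpoints is applied to costs, the comparison is selected on the effectiveness outcome, and the additional imputation leaves out deaths.

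Under a constant hazard, about 29% of arm A and 11% of arm C would be expected to lack a follow-up value at the planning rates. Under the revised difference it is about 22-29% versus 11-16%. These figures rest on the planned effect and on the assumed timing of events. The direction and size of any resulting bias depend on how care time changes before an event, which the article does not give, so no Euro figure should be attached to it.

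**What to change.** **Analysis.** For informal care in the cost-effectiveness analysis, replace the available-case rule with cost accumulated up to each patient's event date, for every enrolled patient and including those who died:
- Predict care between the last interview and the event from the interview values, baseline Barthel and NOSGER scores and the insurance data.
- Set home care to zero after placement or death, so that no imputation adds home care that was not given.
- Report sensitivity to flat, rising and falling care before the event.

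If the full analysis plan already does this, it is enough to say so.

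**Reporting.** State the unobserved pre-event period as a limitation. Care-time items at the placement contact would have been cheap, but the Background section reports that follow-up has ended, so they can serve only a future study.

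**Cost.** One extra cost model on data already collected. Its results rest on assumptions about a period that was not observed, most heavily for patients whose event fell in year 1, and the sensitivity analyses should make this visible.
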